**Fig. 1 Fig1:**
[figure not shown]
The procedure for assessment of needle placement

Using Bowen et al.’s framework [15], Table 6 presents all the measures for which data are to be collected to inform the feasibility evaluation. The researcher will diarise events for the feasibility assessment, such as noting whether the protocol was adhered to by nurses (e.g. use of ultrasound) and patients (attendance and compliance with use of ultrasound). Feasibility assessment data will be collected via a structured survey at the completion of the data collection for all needle placement measurements. A semi-structured interview or focus group will be held following completion of the cannulation data collection phase to capture nurses’ perceptions of the feasibility of use of point-of-care ultrasound for routine cannulation. Questions will be asked in relation to ease of use, fit within the culture of the unit, barriers and facilitators, and suggestions for future implementation.

### Data analysis

Patients’ demographic and clinical data and nurses’ demographic and experience data will be reported as means and standard deviations or frequencies and proportions. The overall study feasibility, implementation feasibility, and acceptability will be reported using descriptive statistics. For feasibility, we will report the proportion of patients/nurses eligible for the study, the proportion of patients/nurses enrolled among those eligible, the reasons for declining participation, the proportion of patients/nurses completing the study, and the reasons for completing or not completing the study.

The implementation feasibility will be reported according to patients’ and nurses’ protocol adherence rate, the proportion of time that nurses adhered to the protocol, and the image assessor’s self-reported confidence regarding the accuracy of their measurements (Likert scale). Acceptability will be reported as the proportion of patients expressing satisfaction and the nurse satisfaction survey results related to the cannulation technique and use of point-of-care ultrasound-guided cannulation. Other data related to extravasations and nurse cannulation and ultrasound experience will be summarised using rates and proportions.

Data collected from semi-structured individual and focus groups interviews will be audio-recorded, transcribed verbatim, de-identified, and undergo content and thematic analyses based on a naturalistic inquiry approach.

The potential effect of the POCUS-guided cannulation on the clinical outcomes (miscannulations [0, 1, 2]), location of the needle in the vessel, and duration of the procedure will be estimated using generalised linear mixed models with link and distribution selected based on the type of outcome. The models will include the patient and nurse as random effects, and the condition, period (order in the sequence), and first carry-over effect as fixed effects.

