## Methods/design

### Aims

The overall aims of this project are to (1) examine the feasibility of the study design and acceptability to nurses and patients of the use of POCUS for guided (dynamic) cannulation in haemodialysis patients and (2) promote successful needle insertion for patients undergoing haemodialysis. These overall aims inform specific methodological and clinical aims, respectively, (1) to assess the feasibility of the proposed design and processes and inform sample size calculations for a larger multi-site study to test the efficacy of the use of POCUS for haemodialysis cannulation and (2) to determine whether POCUS-guided needle insertion improves successful cannulation and cannulation accuracy.

For the purposes of this research, successful cannulation is defined as the needle for haemodialysis being inserted without miscannulation or manipulation. Miscannulation is defined as the needle requiring reinsertion/replacement as a result of extravasation or misalignment with the vessel lumen. All POCUS-guided insertions will be performed using dynamic real-time ultrasound guidance.

The feasibility of study design and methods for measurement of POCUS-guided cannulation versus blind cannulation will be assessed using the feasibility framework advanced by Bowen et al. [15]. The following aspects will be evaluated: recruitment, retention, and attrition of both patients and nurses; methods of data collection; acceptability by both patients and nurses; and demand, implementation, and integration (see Table 1).

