**Table 1 Tab1:**
[figure not shown]
SPIRIT figure illustrating study events and timings.

*-t*_*1*_ prior to allocation; *t*_*0*_ time zero, at allocation; *t*_*1*_ time 1, after the first ultrasound cannulation; *t*_*2*_ time 2, after each cannulation.

To address the first aim (methodological), which is to assess the feasibility of the proposed design and processes and inform sample size calculations for a larger multi-site study to test the efficacy of the use of POCUS guidance for haemodialysis cannulation, the primary outcome measures are:Participation rates of patients and nurses (implementation)Nurse adherence to and usability of POCUS-guided cannulation in haemodialysis (implementation)Procedural time (implementation), patient perceptions of POCUS-guided cannulation (acceptability)Nurse perceptions of POCUS-guided cannulation (acceptability, implementation, integration)

To address the second aim (clinical), which is to determine whether POCUS-guided needle insertion improves successful cannulation and cannulation accuracy, the outcome measures assessed at each haemodialysis session are:Successful cannulation on first attempt of arterial and venous needlesAccuracy of arterial and venous needle tip placementTotal number of extravasationsPatient pain score

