Specific data collected at each haemodialysis session in relation to the nurse cannulator, patient, and dialysis machine are outlined in Table 5. The researcher will observe every cannulation in each treatment session and record the characteristics listed in Table 5 for both the venous and the arterial cannulation. A cannulation will be defined as successful (0) if the needle for haemodialysis is inserted without miscannulation or manipulation, or unsuccessful (1) if the needle extravasates the vessel or blood cannot be accessed from the needle. The number of miscannulations in a session will then take values 0, 1, or 2. For example, a nurse cannulates with the first (arterial) needle and extravasates the vessel, the needle is removed, and pressure applied to the site. This is recorded as ‘1’. In a second attempt, the arterial needle is appropriately placed in the vessel, i.e. it is successful, so this is recorded as ‘0’. The venous needle is also inserted successfully and recorded as ‘0’. The total number of miscannulations for this patient would be ‘1’. In consultation with management of the dialysis unit, the maximum allowable number of blind cannulations for a patient treatment is set at four, a maximum of two cannulations per site. For example, if a nurse miscannulates twice on the arterial point using the standard practice of blind cannulation, they would then use POCUS guidance to cannulate the third time. This information will be recorded by the researcher observing the process. If the cannulator deems POCUS guidance necessary after one miscannulation, this is acceptable and will be documented as above.

**Table 5 Tab5:** Data collected during the study

Nurses	Patients	Dialysis machine
Sitting or standing to cannulate	Patient arm position	Pump speed (Qb)
Use of gloves (sterile or non-sterile)	Patient-reported pain score (scales 1–10) each needle	Venous and arterial line pressures
Ultrasound probe held longitudinal or transverse	Patient-reported perception of the cannulation experience (scales 1–10)	Any initial pressure alarms
Cannulate in one or two motions	Patient additional comments re-cannulation or ultrasound process	
Needle manipulation once inserted	Ultrasound images in both transverse and longitudinal planes	
Time from tourniquet application until machine started		
Miscannulations (needle removed and re-sited)		
Nurse-reported perceptions of the use of ultrasound

**Table 6 Tab6:** Feasibility assessments

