Tool	Assessing	Participants	Time period
Structured observational tool	Implementation: participation rates (number of participating patients or nurses related to number of eligible patients or nurses). Overall recruitment, retention, and questionnaire completion rates	Patients Nurses	Throughout the data collection phase
Patient satisfaction survey	Acceptability: patient satisfaction with cannulation technique, use of point-of-care ultrasound	Patients	After each cannulation
Nurse satisfaction survey	Acceptability: nurse satisfaction with cannulation technique and use of point-of-care ultrasound	Nurses	After first cannulation with ultrasound After the half way point of the cannulation data collection
Researcher study notes (diary)	Implementation: protocol adherence by nurses; issues verbalised by nurses, other staff, or patients regarding the study protocol, reasons for drop-out for both patients and nurses	Patients and nurses	Throughout data collection phase
Image assessor measurement survey	Implementation: image assessor’s confidence in accuracy of measurements	Image assessor	Following completion of all needle placement measurements
Structured interview or focus group	Acceptability, demand, implementation, and integration: suitability, usability, barriers and facilitators, sustainability	Nurses	Following completion of the cannulation data collection phase

Once haemodialysis is started, the vascular access nurse expert, using the Terason uSmart 3200 T ultrasound, will take static ultrasound images in both transverse and longitudinal planes, save the images to a portable storage device, and print them for image assessor review.

A third person (image assessor), who is experienced in renal vascular access, will review the images and record data on needle positioning. The image assessor will be blinded to patient, nurse, and condition and will measure (with a ruler) the location of the needle relative to the right and left side (transverse image only) of the vessel and the top and bottom of the vessel (transverse and longitudinal images). The image assessor will complete a short, structured survey at the end of the data collection phase to capture their perceptions about the ease of conducting measurements, the image quality, and their confidence in accuracy of their measurements (see Fig. 1).

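### Patient acceptability is reported as one proportion with no condition named, and the perception and pain scores are left out of the models that estimate the condition effect

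*Protocol article*

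**What the plan says.** All references are to the protocol article.

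- **Aim and outcome.** Under Aims, the first aim includes "acceptability to nurses and patients of the use of POCUS for guided (dynamic) cannulation in haemodialysis patients". The primary outcome list after Table 1 contains "patient perceptions of POCUS-guided cannulation (acceptability" as an acceptability measure. The list for the second, clinical aim in the same place includes the patient pain score.
- **Collection.** Table 6 gives the object of the patient satisfaction survey as "Acceptability: patient satisfaction with cannulation technique, use of point-of-care ultrasound" and its timing as "After each cannulation", with no restriction to POCUS sessions. Table 5 adds "Patient-reported perception of the cannulation experience (scales 1–10" and a pain score for each needle, both recorded per session.
- **Design.** Every nurse meets every patient twice, once in each condition, and each patient is described as his or her own control.
- **Analysis.** Data analysis says that "acceptability will be reported using descriptive statistics" and then: "Acceptability will be reported as the proportion of patients expressing satisfaction". The model sentence starts with miscannulations and goes on to "location of the needle in the vessel, and duration of the procedure will be estimated using generalised linear mixed models". These models have patient and nurse as random effects, and condition, period and first carry-over as fixed effects.
- **Abstract.** The Methods paragraph lists patient and nurse perceptions among the clinical outcomes and says that clinical outcomes go into generalised linear mixed models.

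**The concern.** Patient perception of POCUS is one of the primary outcomes of the feasibility aim. It is measured repeatedly in each patient under both conditions, but its stated summary does not name a condition. A reader of the eventual report could take a high proportion as acceptance of POCUS when part of it may come from blind sessions.

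The crossover is justified by within-patient control. The stated models use that control for three outcomes and not for the patient-reported scores, which are collected in the same sessions. The Abstract and Data analysis also disagree on whether patient perceptions are modelled at all. Since the study is meant as a template for a multi-site trial, the ambiguity would carry over into it.

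**Working it through.** The article gives no numerical figure for this outcome, so there is none to reproduce. The check has three parts.

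**1. What the design yields.** Inputs: 20 patients and 10 nurses (Target sample size), and two conditions per patient–nurse pair (Design).

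- Sessions: 20 × 10 × 2 = 400.
- Per condition: 20 × 10 = 200.
- Per patient: 10 × 2 = 20 ratings, 10 under POCUS and 10 blind.

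These are maxima. The Design section says up to 20 patients, and attrition is expected.

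**2. What an unsplit proportion can say about POCUS.** Suppose, as an assumption, that the proportion is taken over ratings and that each condition supplies the same number. Let P be the overall proportion satisfied, p₁ the POCUS proportion and p₀ the blind proportion. Then

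P = (p₁ + p₀) / 2, so p₁ = 2P − p₀.

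Because p₀ lies between 0 and 1, p₁ lies between max(0, 2P − 1) and min(1, 2P). The difference is p₁ − p₀ = 2(p₁ − P).

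| Overall P | Possible p₁ | Possible p₁ − p₀ (points) |
|---|---|---|
| 75% | 50% to 100% | −50 to +50 |
| 80% | 60% to 100% | −40 to +40 |
| 90% | 80% to 100% | −20 to +20 |

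For P = 0.80: the lower limit is 2 × 0.80 − 1 = 0.60 and the upper is min(1, 1.60) = 1. The differences are 2 × (0.60 − 0.80) = −0.40 and 2 × (1 − 0.80) = +0.40. A pooled 80% therefore does not fix even the sign of the difference.

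**3. The sections side by side.**

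| Outcome | Abstract, Methods | Data analysis |
|---|---|---|
| Patient perceptions | Clinical outcome; clinical outcomes go to mixed models | Acceptability descriptive; not named in the model sentence |
| Pain score (clinical outcome in the list after Table 1) | Not named | Not named in the model sentence or elsewhere in the section |

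The first row is a conflict within the article. The second is a declared outcome of the clinical aim that the stated analysis does not take up. Both scores exist for each session with a known allocated condition, so the planned model can take them without change to its structure. Its link and distribution are already to be chosen by outcome type.

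One further feature affects how blind sessions are read. The data collection section allows POCUS to be used within a blind session after miscannulation and has this recorded. Some ratings from sessions allocated to blind cannulation will therefore follow actual use of ultrasound.

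**The case against.** The strongest reply is that the acceptability aim is not comparative. It asks whether POCUS is acceptable, not whether patients prefer it, and the Discussion says the study will not give effectiveness results. A descriptive proportion among POCUS sessions would answer that aim. This stands, and no formal test should be asked for. The analysis sentence does not, however, state that restriction.

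A reader might infer that the plan merges POCUS and blind ratings. The text does not say so. The sentence goes on to the nurse survey and closes with a phrase on technique and ultrasound use that may govern the patient proportion too. Even then, technique covers both conditions, so the condition remains unnamed. The bounds above show what pooling would do; they do not show that it is planned.

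A reader might also infer that the study cannot show how patients rate POCUS against blind cannulation. That is too strong. The ratings are collected by session and allocated condition, the Abstract points to a model, and the Design section plans patient interviews after each session that look for differences in responses.

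Nor is the small sample the defect. With 16 of 20 satisfied, the Wilson 95% interval is 58% to 92%, but that is ordinary pilot imprecision and has nothing to do with the missing split.

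Finally, the cut-off for satisfied and the rule for combining a patient's repeated ratings may properly sit in a full protocol or SAP, and they are not counted here. The conflict between two sections of one article, and a model list that omits a declared clinical outcome, are not of that kind.

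**Conclusion.** The point holds as a minor one. Data analysis gives patient acceptability as a proportion without a named condition. It leaves the perception and pain scores out of the condition-effect models, and on perceptions it disagrees with the Abstract. The stated analysis thus does not use the within-patient contrast for patient-reported outcomes, although the design supplies up to 10 ratings per patient in each condition.

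If ratings were pooled in equal numbers, 80% satisfied would be compatible with POCUS satisfaction from 60% to 100%. That range rests on the assumptions of pooling, of equal numbers per condition and of ratings as the unit, none of which the article states. The omission of pain and the conflict between the sections rest on the text alone.

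**What to change.** 1. Make the Abstract and Data analysis agree on whether patient perceptions are modelled.
2. Report the proportion satisfied separately for sessions allocated to POCUS and to blind cannulation. Flag descriptively the blind sessions in which POCUS was used after miscannulation.
3. Add the 1–10 perception score and the per-needle pain score to the planned mixed model. Report the within-patient POCUS-minus-blind estimate by allocated condition with its confidence interval, labelled as estimation and not as a formal test.

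The cost is a few sentences and two more outcomes in a model already planned, on data already to be collected. The downside is slightly more analysis and reporting.

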### Target sample size

The target sample size will be 20 patients (based on 30 patients attending the unit with an AVF in situ) and 10 nurses (based on 20 nurses working in the unit). It is estimated that data collection will take place over 12 months. This timeframe is based on a calculation of 10 part-time nursing staff on a rotating roster and takes into account sick and annual leaves and potential patient attrition throughout the study. Nurses will complete both POCUS-guided and blind cannulations on all patients participating in the study in the timeframe.

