### Data collection, outcome measures, and procedures

Data collection and management will proceed in accordance with the SPIRIT guidelines as represented in the SPIRIT figure in Table 1.

Baseline demographic data will be collected via a survey (Table 2).

**Table 2 Tab2:** Baseline data collected at enrolment

Nurses	Patients
Age	Age
Sex	Sex
Dominant hand	Type of AVF
Years of experience in dialysis	Comorbidities
Years of experience with cannulation	Other relevant medical history
Years of experience with ultrasound	Time on haemodialysis
Employment status (full- or part-time)	Frequency of haemodialysis
Completed level of education	Date of AVF creation and first cannulation
Completion of formal or informal ultrasound training	
Frequency of use of ultrasound use to assess AVFs	
Frequency of use of ultrasound to guide cannulation	
Circumstance that prompt to use the ultrasound for guidance	

Nurse participants working at the study site undertake ultrasound competency training on employment and are encouraged to regularly use static POCUS assessment prior to cannulation. The competency training with a vascular access expert involves one training session using ultrasound guidance on training models (namely chicken fillets filled with water balloons).

The aim is for two nurse participants on each morning shift and two nurse participants on each afternoon shift to cannulate two patient participants each during the study. This schedule will capture eight patients per day, 16 patients per week. The patient and nurse participants are each assigned a number (1, 2, 3, etc.) by the researcher based on recruitment order. A statistician, who only knows the total number of patient and nurse participants, will arrange them into dyads via Excel spreadsheet and randomly assign each dyad an allocated condition (POCUS or blind) to be undertaken at first meeting of that dyad (Table 3). At the next meeting of the dyad, the opposite condition would apply (Table 4). Due to the time periods between treatment cannulations and the use of the best practice rope ladder cannulation technique practiced by staff in the unit, evidence of needle placement following use of ultrasound in one session is not anticipated to influence the blind cannulation needle placement in the next session. It is estimated that data collection will take approximately 12 months depending on staff and patient availability.

**Table 3 Tab3:** Example of patient and nurse allocation to condition

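### The stated random effects omit the patient-nurse dyad and name no nurse-by-condition term, so the standard error of the POCUS effect and the variances carried into planning can be off in either direction.

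*Protocol article*

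**What the plan says.** The Data analysis section plans generalised linear mixed models for three clinical outcomes: miscannulations per session, needle location and procedure duration. It states that "The models will include the patient and nurse as random effects", with condition, period and first carry-over as fixed effects. No dyad, session or nurse-by-condition term appears.

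Under Data collection, outcome measures, and procedures, the statistician forms patient-nurse dyads and will "randomly assign each dyad an allocated condition (POCUS or blind) to be undertaken at first meeting of that dyad". Then, "At the next meeting of the dyad, the opposite condition would apply". The Design section describes allocation somewhat differently, as balanced sequences to which patients are randomly assigned, but it too has each nurse meet each patient once under each condition. On either description a complete dyad supplies one POCUS session and one blind session.

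The target is 20 patients and 10 nurses (Target sample size). On the units of measurement, the observer will "record the characteristics listed in Table 5 for both the venous and the arterial cannulation", but the miscannulation outcome is a session total: "The number of miscannulations in a session will then take values 0, 1, or 2". Table 5 gives one procedure time per session.

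Table 2 records each nurse's years of ultrasound experience, training and frequency of ultrasound-guided cannulation. The Aims include informing the sample size of a larger multi-site study.

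**The concern.** Two features of the design have no counterpart in the stated model.

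- **Dyad.** Each dyad is its own control. Anything peculiar to one nurse working on one patient's fistula is shared by that dyad's two sessions and drops out of the difference between them. Without a patient-by-nurse effect, the model counts that variation as residual noise. The standard error and the residual variance handed to the next trial can then be too large.
- **Nurse variation in benefit.** The Design section relies on nurse factors, ultrasound experience included, being balanced across patients. Balance removes nurse main effects from the comparison. It does not remove differences between nurses in how much POCUS helps. That variation is averaged over only 10 nurses, and more patients per nurse do not reduce it. If it is left out, an interval meant to apply to other nurses can be too narrow, and a variance that multi-site planning needs is never estimated.

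**Working it through.** **Inputs from the protocol.** 20 patients, 10 nurses, 2 sessions per dyad: 20 × 10 = 200 dyads and 400 sessions. The stated throughput reproduces: 2 shifts × 2 nurses × 2 patients = 8 per day, and × 2 days = 16 per week. The target sample size has no alpha, power, effect or SD behind it, so there is no power figure to reproduce.

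**Assumptions.** The protocol gives no variance components. The residual variance is set to 1, and the others are varied: dyad variance σd², and variance of nurse-specific POCUS effects τ². The layout is complete, the outcome continuous, and period and carry-over terms are left out.

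**Formulas.** The additive model has 400 − 1 − 19 − 9 − 1 = 370 residual df. Of these, 171 carry patient-by-nurse variation and 9 carry nurse-by-condition variation. With σnc² = τ²/2:

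- E[MSres] = 1 + (171 × 2σd² + 9 × 20σnc²)/370
- model SE = √(2 × E[MSres]/200)
- true SE = √(2/200 + τ²/10)
- coverage = 2Φ(1.96 × model SE / true SE) − 1

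**Dyad omitted, no nurse variation (true SE 0.100).**

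| σd² | E[MSres] | model SE | ratio | coverage |
|---|---|---|---|---|
| 0.1 | 1.092 | 0.105 | 1.05 | 95.9% |
| 0.25 | 1.231 | 0.111 | 1.11 | 97.0% |
| 0.5 | 1.462 | 0.121 | 1.21 | 98.2% |

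The E[MSres] column is the residual variance that would go into planning; the within-dyad value is 1.

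**Nurse variation omitted, no dyad variance.**

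| τ | E[MSres] | model SE | true SE | coverage |
|---|---|---|---|---|
| 0.25 | 1.015 | 0.101 | √0.01625 = 0.127 | 88% |
| 0.5 | 1.061 | 0.103 | √0.035 = 0.187 | 72% |

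The nurse term is 0.00625/0.01625 = 38% of the true variance at τ = 0.25 and 0.025/0.035 = 71% at τ = 0.5.

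**Both omitted.** With σd² = 0.5 and σnc² = 0.02 (τ = 0.2): E[MSres] = 1 + (171 + 3.6)/370 = 1.472, model SE 0.121, true SE √0.014 = 0.118, ratio 1.03, coverage 95.6%. Here the errors nearly cancel. With all omitted components at zero, coverage is 95.0%.

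**0/1/2 counts.** 2,000 simulated datasets per setting were analysed with a linear approximation, not a fitted mixed model, at baseline logits of −2.2 and −1.4 (about 10% and 20% miscannulation per needle).

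- Dyad SD 1.0 on the logit scale, no nurse variation: SE 0.0519 against an empirical 0.0467, and 0.0624 against 0.0555; coverage 97.2% and 97.5%.
- Nurse-effect SD 0.5 without dyad variance: coverage 88.0% and 85.2%. At SD 1.0: 74.7% and 68.8%.
- An interval from the 10 nurse-level differences (t, 9 df) covered 94% to 96% throughout.

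**Two needles.** If needle location is analysed with one row per needle and no session effect, model SE / true SE = 1/√(1+ρ). For within-session correlation ρ of 0.1, 0.3 and 0.5 this is 0.95, 0.88 and 0.82, with coverage of 93.8%, 91.4% and 89.0%.

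**The case against.** The strongest reply has four parts.

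- **Wording.** The article speaks of random effects, not of random intercepts alone, and a fuller analysis plan may exist. This stands in part: a condition slope by nurse is not excluded. But the model statement is detailed enough to include a carry-over term, and no reading of it supplies a dyad effect.
- **Needles.** A reader might infer that the two needles of a session are treated as independent throughout. The protocol does not support that. Miscannulations are modelled as a session total and duration is one value per session. Only needle location could be affected, and the article does not say whether it uses one row per needle.
- **Sparse counts.** The audit in the Background found 5 to 25 miscannulations a month. If that unit is the study unit, and its 30 fistula patients dialyse three times weekly, there are 30 × 3 × 52/12 = 390 sessions a month. That is about 1.3 to 6.4 events per 100 sessions, or roughly 5 to 26 in 400 sessions if POCUS makes no difference. Dyad and slope variances would be barely estimable from so few events. This stands and limits the fix. These rates are also well below those simulated, so the count results are only illustrative.
- **Stakes.** The Discussion says the pilot will not settle effectiveness. True, but the Aims make it a source of planning inputs, so the variance components matter as much as the estimate.

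It would also go too far to say that the pairing is wasted. In the complete layout, with period and carry-over set aside, the additive model's estimate is still the mean within-dyad difference. Omitting the dyad affects the standard error and the residual, in the conservative direction.

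**Conclusion.** The stated model does not match the design in one definite respect, the missing dyad effect, and on its ordinary reading in a second, the missing nurse-by-condition effect. The first can overstate the standard error by about 5% to 21% and the planning residual variance by about 9% to 46%, for dyad variance of 0.1 to 0.5 of the residual. The second can reduce coverage to about 88% or 72%, for nurse-specific effects with an SD of 0.25 or 0.5 residual SD, when inference is meant to reach beyond these 10 nurses.

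A reader might conclude that the intervals and variances will be wrong. The documents do not support that. They give no variance components, the error vanishes if the omitted components are zero, and the two errors pull in opposite directions. Cancellation in one standard error would not repair the planning inputs, however: the residual would still be inflated and the nurse-by-condition variance still unknown. The change is worth making before analysis. It does not undermine the trial's conduct or data.

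**What to change.** In Data analysis:

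1. Add a random patient-by-nurse (dyad) effect alongside patient and nurse.
2. For duration and needle location, also add a random nurse-by-condition effect, use Kenward-Roger or Satterthwaite degrees of freedom, and report all variance components.
3. State whether needle location has one row per needle. If so, add a session effect. This is not needed for the session count or for duration.
4. For the miscannulation count, keep the model simple, with no nurse slopes, and say in advance what happens if the dyad variance cannot be estimated. As a sensitivity analysis, give an interval from the 10 nurse-level POCUS-minus-blind differences (t, 9 df), or a nurse-clustered interval with a small-sample correction. An uncorrected one would be unreliable with 10 clusters.

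The cost is a few sentences and some programming, with no change to randomisation, visits or data collected. Intervals may widen if the effect varies by nurse, and variance components from 10 nurses will be imprecise, so they should be carried into planning as ranges.
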